## Methods

### Design and Study Setting

This multicenter phase II rater-blinded randomized controlled trial will involve the participation of four different centers in Catalonia: Hospital Parc de Salut Mar, Vic Hospital Consortium, University Hospital Mutua of Terrassa and Althaia Xarxa Assistencial Universitària of Manresa. The Hospital Parc de Salut Mar is a center of reference for mental health treatment and research, among other disciplines, and the collaboration with the rest of the institutions will ensure the recruitment of the complete sample.

Participants will be randomized to either treatment as usual (TAU) or to 20 individual 60-minute EMDR sessions over 5 months, as well as TAU. EMDR therapists participating in this trial are highly experienced, have received advanced training in EMDR protocols, and were recruited through face-to-face interviews. Assessments will be carried out at three time points: baseline (T0), post-treatment at 6 months (T1) and at 12-month follow-up (T2) (see **Table 1**). The clinical raters carrying out evaluations will be blind to the participants’ research condition; however this is not a double-blind study as it is not possible to mask from the patient whether they are undergoing EMDR therapy or not due to its use of bilateral stimulation.

**Table 1 T1:** SPIRIT Flow diagram: Schedule of enrolment, interventions and assessments.

Timepoint**	Study Period			
	Enrolment	Allocation	Post-allocation	Close-out
*-t_1_ & t_0_*	0	*T_1_*	*T_2_*

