### Hypotheses

1. Patients in the EMDR group will show fewer relapses compared to the control group after therapy (T1) and at the 12-month follow-up visit (T2).2. Patients in the EMDR group will show fewer psychiatric and trauma-related symptoms compared to the control group after therapy (T1) and at the 12-months follow-up visit (T2).3. Patients in the EMDR group will improve their functional capacity in comparison to the control group at evaluations after therapy (T1) and at the 12-months follow-up visit (T2).4. Patients in the EMDR group will show a better adherence to pharmacological treatment in relation to the control group after therapy (T1) and at the 12-month follow-up visit (T2).

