### Statistical Analysis

The distribution of socio-demographic, clinical (including psychological trauma), functionality, quality of life and treatment adherence characteristics among baseline groups will be analyzed using descriptive statistics. Continuous variables with a normal distribution will be analyzed with the Multivariate Variance Analysis. The change of the clinical variables of functionality and quality of life with respect to the baseline assessment at strategic points of the intervention will be analyzed by ANOVA with repeated measurements, including time factors, treatment conditions and their interaction. For those cases in which the premises of normality are not fulfilled, the Wilcoxon test will be used. The differences between groups, for the categorical and main clinical variables, will be analyzed by means of the Chi-square test. Those variables that are statistically significant can be used as covariates for a logistic or linear regression study of the factors associated to the magnitude of the effect and determine which variables are the best predictors of functioning. The effect size index (Hedges g or r de Pearson index) will be estimated in case of correlation indexes of each of the analyses performed. The statistical software used for the analyses will be the latest available version of the SPSS (v. 23).

For the main statistical analysis, we will conduct an intention-to-treat (ITT) analysis. We will impute lost to follow-up with the Last Observation Carried Forward (LOCF) method.

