### Dropouts and Follow-Up

Any patient who is admitted to hospital following a clinical relapse during the 5-month intervention period will be considered to be dropout and will be excluded from the trial. In the case of relapse during follow-up, patients will be removed from the study and relapse-related factors will be collected for subsequent analysis.

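### Relapse ends scale assessment, so T2 scores are missing because of the main outcome; neither LOCF nor omitting these patients gives a sound T2 comparison

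*Protocol article*

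**What the plan says.** Under Dropouts and Follow-Up, two rules apply. A patient hospitalised for relapse during the five-month intervention "will be considered to be dropout and will be excluded from the trial". For later relapses: "In the case of relapse during follow-up, patients will be removed from the study and relapse-related factors will be collected for subsequent analysis". No scale assessment after relapse is mentioned.

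Under Statistical Analysis the protocol says "For the main statistical analysis, we will conduct an intention-to-treat (ITT) analysis", followed by "We will impute lost to follow-up with the Last Observation Carried Forward (LOCF) method". This is the only missing-data rule, and it makes no exception for relapse.

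Design and Study Setting puts assessments at T0, T1 (6 months) and T2 (12-month follow-up). Tables 2 to 4 schedule the symptom, functioning, quality-of-life and drug-attitude scales at all three. Hypotheses 2 to 4 compare the arms on symptoms, functioning and adherence at T1 and T2. Change in functioning and quality of life "will be analyzed by ANOVA with repeated measurements, including time factors, treatment conditions and their interaction".

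**The concern.** Relapse is the main outcome, and it is also what stops the scale measurements. The missing T2 scores are therefore informative by design: they belong to patients known to have deteriorated. The analysis section promises to keep every randomised patient, while the dropout section takes out the patients whose T2 scores matter most. Nothing in the article reconciles the two.

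At stake are the T2 comparisons in hypotheses 2 to 4. The Discussion names the one-year follow-up as the study's strength because it tests whether gains last. If a T1 score is carried over a relapse, the gain lasts by construction in that patient. A later analysis plan could replace LOCF, but it could not recover scores that were never collected.

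**Working it through.** The plan gives no figure on this point to reproduce. The check is to follow the two rules through and then size the effect under stated assumptions.

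**Step 1: which score reaches T2.**
- Relapse between T1 and T2: the last score is T1, taken before the relapse.
- Removal or exclusion before the six-month visit: the last score is T0. This is not a well score, since entry requires a first psychotic episode within the past year, IES-R above 0 and SUD above 5 (Participants).

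**Step 2: the two possible readings.**
- Removed patients count as lost to follow-up: LOCF puts the scores from step 1 into the T2 analysis.
- Removed patients are left out: the analysis is no longer intention-to-treat, and T2 compares only patients selected on a post-randomisation event.

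**Step 3: size under LOCF, for relapses between T1 and T2.** Let p be the relapse risk in an arm and D the worsening still present at T2, equal in both arms, with no other average change from T1 to T2.
- True T2 mean in an arm = T1 mean + p × D.
- LOCF T2 mean in an arm = T1 mean.
- Each arm mean is too favourable by p × D.
- The between-arm difference loses (p in TAU − p in EMDR) × D.

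PANSS illustration (all inputs assumed, none from the documents): 30% relapse in TAU, 15% in EMDR.
- D = 20: TAU 0.30 × 20 = 6.0, EMDR 0.15 × 20 = 3.0; lost difference 0.15 × 20 = 3.0 points.
- D = 15 to 25: 0.15 × 15 = 2.25 to 0.15 × 25 = 3.75 points.
- Half of the 20 points resolved by T2: 0.15 × 10 = 1.5 points.
- Risks reversed: the same 3.0 points, now to the disadvantage of EMDR, are lost.
- Equal risk and severity: 0 lost from the difference, but both means are still too favourable by p × D.

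In SD units, with 40 per arm (from the protocol), assumed TAU risks, and a hazard ratio of 0.5 (the reciprocal of the protocol's design value of 2), EMDR risk = 1 − (1 − TAU risk)^0.5. D is assumed to lie between 0.5 and 1.5 SD.

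| TAU risk | EMDR risk | Relapsers TAU / EMDR | Lost difference, D = 0.5 to 1.5 SD |
|---|---|---|---|
| 15% | 7.8% | 6.0 / 3.1 | 0.04 to 0.11 |
| 25% | 13.4% | 10.0 / 5.4 | 0.06 to 0.17 |
| 40% | 22.5% | 16.0 / 9.0 | 0.09 to 0.26 |

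Across these cases the TAU mean is too favourable by 0.075 to 0.60 SD and the EMDR mean by 0.04 to 0.34 SD.

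**Step 4: would a better imputation method alone help?** No. If no relapser has a T2 score, a missing-at-random model learns the T1-to-T2 relation from non-relapsers only. In the set-up of step 3 it predicts T2 = T1 on average for relapsers, so it also loses 3.0 points in the PANSS example. Adding relapse status as a predictor does not help, because its effect on T2 cannot be estimated without observed T2 scores in relapsers.

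**The case against.** The strongest reply is that the article never says that removed patients count as lost to follow-up. A reader might infer that relapsers certainly enter T2 by LOCF. The text does not prove that, and exclusion is an equally literal reading. This stands, but it does not rescue the plan, because exclusion contradicts the stated intention-to-treat analysis.

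A reader might also infer that relapsers are always scored as well. For those who leave before T1 this is wrong: their carried score is the symptomatic T0.

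A third inference would be that LOCF erases the EMDR benefit or hides harm. That goes too far. Only the part of the T2 effect that runs through relapse is lost. A T1 benefit, and a T2 benefit in non-relapsers, remain. Relapse is the main outcome and relapse-related factors are collected, so an excess of follow-up relapses under EMDR would still show there. The 3.0-point example also depends on the full worsening persisting to T2.

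Finally, LOCF may be blamed as the cause. The root is that assessment stops at relapse; LOCF is one of two unsound ways to deal with the gap.

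**Conclusion.** The concern holds in this form: the dropout rule makes T2 scale data missing because of the main outcome, and neither available reading of the analysis section gives a valid intention-to-treat comparison at T2. Under LOCF the T2 difference loses about the difference in relapse risk times the worsening still present. In the assumed examples this is 1.5 to 3.75 PANSS points, or 0.04 to 0.26 SD. These sizes rest on assumed relapse risks and severity, equal severity in both arms and no other mean change from T1 to T2. The mechanism does not depend on the particular values.

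The direction is not fixed. If EMDR lowers relapse, its T2 benefit is understated; if it raises relapse, the T2 disadvantage is understated; if risk and severity are equal, only the arm means are distorted. The consequence demonstrated here is limited to the secondary T2 comparisons. It should still be corrected early, because unmeasured scores cannot be recovered.

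**What to change.** 1. Reconcile Dropouts and Follow-Up with Statistical Analysis so that relapse, in either period, does not end study assessments. This concerns data collection only and leaves treatment decisions open.
2. Assess relapsed patients at the scheduled T1 and T2 visits and use those scores in the intention-to-treat analysis.
3. With those data in hand, replace LOCF as the main method by a mixed model, or by multiple imputation that uses relapse status, for scores that are still missing. Keep LOCF as a sensitivity analysis at most. Without step 2, this step does not remove the bias.
4. Analyse time to relapse with censoring at last contact, not with imputed values.

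The cost is revised wording and attendance of relapsed patients at visits that are already scheduled. Some of them may be hard to assess, so some T2 scores will remain missing.

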## Stepwise Procedures

### Intervention

#### EMDR

The patients in the EMDR arm of the study will receive a maximum of 20 individual 60-minute sessions, using the standard EMDR therapy protocol to treat past trauma-related symptoms developed by Francine Shapiro (34) and the Recent Traumatic Episode Protocol (R-TEP) protocol developed by Elan Shapiro (35).

Here is a brief description of the most recent eight-phase standardized protocol:

Patient history: The therapist collects information regarding the patient’s biography, including attachment history, medical history, physical health, as well as traumatic events experienced and their relationship to current symptoms, in order to develop a treatment plan.Patient preparation: Following an explanation of EMDR therapy, the therapist checks the patient’s tolerance to different types of bilateral stimulation, primarily side-to-side eye movements, but where these are not tolerated, tapping of the patient’s hands or auditory tones can be used. Positive resources for emotional regulation are installed.Patient assessment: A traumatic memory is chosen as a therapeutic target and the therapist assists the patient in identifying the image representing the worst part of the memory and its associated cognitions, emotions and corporal sensations. The patient then rates their current level of distress using the Subjective Units of Disturbance Scale (SUD), ranging from 0 (neutral or minimum disturbance) to 10 (maximum disturbance).Memory desensitization: While the patient focuses on the traumatic image and associated negative cognition, emotions and physical sensations, 30–40 second sets of bilateral stimulation (e.g. through side-to-side eye movements) are applied, during which the patient observes without judgment their thoughts, and after each set tells the therapist what they observed. The therapist does not comment, instead applying further sets until the patient has processed the traumatic memory and their subjective distress is at 0 on the SUD scale.Installing the positive cognition: The patient now focuses on the original traumatic memory and a positive cognition which is the opposite of the negative cognition originally generated by the traumatic memory, and further sets of bilateral stimulation are applied to install the new positive belief.Body scan: While focusing on the original memory and positive belief, the patient is asked to scan their body and notice if there are any physical sensations. If there are any negative sensations, bilateral stimulation will be continued until they disappear. If there are positive sensations, short 10–12 second sets of bilateral stimulation will be applied to reinforce them.Closure: At the end of the session, the therapist explains possible post-session effects, which can include new insights, memories or dreams, and what to do should these occur.Reevaluation: In the following session, the therapist checks that the memory has been successfully processed and desensitized before selecting either a new traumatic memory, current trigger of distress, or potentially threatening future event to work on.

The Recent Traumatic Episode Protocol (R-TEP) developed by E. Shapiro and Laub (35) is used in this study for the treatment of a recent trauma. This protocol is a new comprehensive protocol which extends from the main protocol of F. Shapiro (34) for recent trauma with additional measures for containment and safety.

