**Conclusion:**

This study will provide evidence of whether EMDR therapy is effective in reducing trauma and clinical symptoms, reducing relapses and in improving functionality and quality of life in patients with FEP and a history of trauma.

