### Participants

The study sample will consist of 80 outpatients fulfilling criteria for a diagnosis of Schizophrenia or Schizophrenia Spectrum, Major Depressive Disorder with psychotic symptoms, or Bipolar I Disorder with psychotic symptoms according to DSM-5 criteria, who had never experienced psychotic symptoms prior to the current episode. The diagnosis of all participants will be carried out by physicians with extensive experience in the diagnosis of FEP.

Inclusion criteria are (1) age between 16 and 65 years at the time of first evaluation; (2) have been diagnosed with a first psychotic episode in the last year, with or without pharmacological treatment and/or psychiatric hospitalization; (3) presence of one or more traumatic events causing trauma related symptoms (Impact of Event Scale-Revised, IES-R >0 and Subjective Units of Distress, SUD >5); 4) ability to read and write in Spanish.

Exclusion criteria are: (1) acute suicidality; (2) presence of organic brain diseases; (3) previous trauma-focused therapy in the past 2 years.

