## Materials and Equipment

### Instruments and Measures

Trauma-related symptoms will be evaluated using the instruments listed in **Table 2**:

Childhood Trauma Questionnaire (CTQ): The CTQ (36), Spanish validation (37), is a self-administered 28-item scale to measure abuse and neglect suffered in childhood on five subscales: emotional, physical or sexual abuse, and emotional or physical neglect, each subscale scored on a 5-point Likert scale. The score for each subscale classifies the severity of the abuse and neglect as: “none to minimal,” “low to moderate,” “moderate to severe” and “severe to extreme”.Global Assessment of Posttraumatic Stress Questionnaire (EGEP-5): The EGEP-5 (38) is a 55-item clinician-applied scale to determine PTSD diagnosis, based on the current DSM-V criteria. This scale consists of three sections: events, symptoms and functioning.The Holmes-Rahe Life Stress Inventory (39); Spanish validation (40) is used to determine which common stressful life events a patient has experienced in the last 12 months, with each life event scored according to a standardized measure of their impact (41) and a total score provided by summing all those applicable to the patient. Although individual characteristics and coping skills should be taken into account when interpreting scores, scores below 150 reflect low levels of stress, scores between 150 and 299 represent a 50% risk of a stress-related illness in the near future and scores above 300 represent an 80% risk (39).Impact of Event Scale - Revised (IES-R): The IES-R (42), Spanish validation (43), is a 22-item self-report measure used to determine the level of subjective distress the subject has experienced over the past week related to a specific stressful life event, with items corresponding directly to 14 of the 17 DSM-IV symptoms of PTSD. Each item is scored on a 5-point Likert scale from 0 to 4, yielding a total score ranging from 0 to 88, with subscale scores for Intrusion, Avoidance and Hyperarousal. Higher scores represent greater subjective distress.Dissociative Experiences Scale (DES): The DES (36), Spanish validation (44), is a 28-item self-report scale which measures the frequency with which an individual experiences a range of dissociative experiences, from normal to pathological. An overall mean score ranges from 0 to 100, and there are subscales for amnesia, dissociation and depersonalization. A total score of over 30 indicate high levels of dissociation.Dissociative Experiences Questionnaire (SDQ-20): The SDQ-20 (45), Spanish validation (46), is a 20-item self-report scale used to measure somatoform dissociation. Each item refers to a physical symptom and is scored from 1 to 5 on a 5-point Likert scale, ranging from “1 = this applies to me not at all” to “5 = this applies to me extremely”, and the patient is then asked if there is a known physical cause. Total scores can range from 20 to 100, with higher scores denoting higher levels of somatoform dissociation.

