
**Table 2 T2:** Measurements to evaluate trauma-related symptoms.

Clinical variable	Measurement interview/self-report	T0 Baseline	T1 Post-treatment 6 months	T2 Post-treatment 12 months
Childhood T.	CTQ	x		
PTSD	EGEP-5	x	x	x
Traumatic events	H-RLSI	x		
Trauma’s impact	IES-R	x	x	x
Dissociation	DES	x	x	x
Somatoform D.	SDQ-20	x	x	x

Childhood T, Childhood trauma; CTQ, Childhood Trauma Questionnaire; PTSD, post-traumatic stress disorder; EGEP-5, Global Assessment of Posttraumatic Stress Questionnaire; H-RLS,: The Holmes-Rahe Life Stress Inventory; IES-R, Impact Event Scale; DES, Scale of Dissociative Experiences; Somatoform D., Somatoform Dissociation; SDQ-20, Dissociative Experiences Questionnaire.

The diagnosis, clinical symptoms and level of functioning are to be assessed using the following instruments (see **Table 3**):

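### Tables 1 and 2 disagree on whether a blind-rated trauma scale (EGEP-5) is repeated at follow-up, and Table 1 instead repeats SUD, the score that EMDR itself works down to 0

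*Protocol article*

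**What the plan says.** **Blinding.** Under Design and Study Setting, "The clinical raters carrying out evaluations will be blind to the participants’ research condition". The same sentence concedes that "it is not possible to mask from the patient whether they are undergoing EMDR therapy or not".

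**Who rates the trauma scales.** Under Instruments and Measures, the IES-R "is a 22-item self-report measure used to determine the level of subjective distress"; DES and SDQ-20 are also described as self-report. The EGEP-5 "is a 55-item clinician-applied scale to determine PTSD diagnosis". SUD is not described in that section. The EMDR section describes it as the patient's own 0 to 10 rating.

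**When they are measured.** Table 1 marks IES-R, SUD, DES and SDQ-20 at enrolment, T1 and T2, and marks EGEP-5 at enrolment only. Table 2, the dedicated table of trauma measures, has the row "PTSD EGEP-5 x x x", that is T0, T1 and T2. It also repeats IES-R, DES and SDQ-20, and has no SUD row.

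**What SUD is used for.** It is part of the entry criterion ("Subjective Units of Distress, SUD >5", jointly with IES-R above 0). It is also the in-session criterion of EMDR: sets of stimulation go on "until the patient has processed the traumatic memory and their subjective distress is at 0 on the SUD scale". In Table 1 it is a T1 and T2 assessment as well. The TAU section rules out any trauma-focused psychological work in the control arm.

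**What the trial will conclude.** Fewer trauma-related symptoms at T1 and T2 form part of hypothesis 2, and post-traumatic stress symptoms are a secondary outcome. The abstract expects evidence of "whether EMDR therapy is effective in reducing trauma and clinical symptoms". Relapse is the main outcome.

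**The concern.** Rater blinding protects a score only if the blinded rater produces it. Patients who know they received up to 20 sessions of an added therapy, compared with patients who know they did not, may report their symptoms differently even if the therapy has no effect. No open psychotherapy trial can remove this, but a trial can schedule at least one outcome scored by someone who does not know the arm. For trauma symptoms, this protocol does so in one table and not in the other.

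SUD adds a separate difficulty. One arm repeatedly gives this rating to a therapist who continues the procedure until it reads 0; the other arm has no such exercise. If the arms are then compared on SUD, part of any difference reflects the procedure itself.

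At stake is the interpretation of the trauma part of hypothesis 2. A site that works from Table 1 would reach T2 with no blind-rated trauma outcome, and this cannot be repaired once the visits have passed.

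**Working it through.** The protocol states no figure on this point, so the check sets its sections side by side.

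**Step 1. Trauma measures repeated at T1 and T2.**

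| Measure | Rated by | Table 1 repeats it | Table 2 repeats it |
|---|---|---|---|
| IES-R | patient | yes | yes |
| DES | patient | yes | yes |
| SDQ-20 | patient | yes | yes |
| SUD | patient | yes | not listed |
| EGEP-5 | clinician | no (enrolment only) | yes |

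- Under Table 1, 4 measures are repeated, 4 are patient-rated and 0 are blind-rated.
- Under Table 2, 4 measures are repeated, 3 are patient-rated and 1 is clinician-applied.

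The tables share three measures and differ on the fourth. That one difference decides whether any trauma outcome at follow-up is covered by rater blinding.

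**Step 2. Which table is meant.** Table 2 is specific to trauma. The abstract names EGEP-5 among the trauma instruments, does not name SUD, and says that all variables are measured at all three time points. That favours Table 2. The abstract's statement cannot be literal, however, because both tables give CTQ and the Holmes-Rahe inventory at baseline only. The intention is likely but not settled.

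**Step 3. SUD in the two arms.** The scale runs from 0 to 10. Entry requires more than 5, so at least 6 on whole points. The EMDR procedure ends desensitization of a memory at 0, which is a fall of at least 6 − 0 = 6 points on any memory rated at entry level and fully processed. This describes an in-session rating of one chosen memory. T1 is at 6 months, after a 5-month intervention, and T2 is at 12 months. The documents do not say which memory the T1 and T2 ratings refer to, how many entry memories are fully processed, or whether a 0 persists. The direction of the effect follows from the procedure; its size at T1 and T2 does not.

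**Step 4. What a reporting shift could do (illustration only).** The documents give no size for reporting bias, so this is an assumed range. Suppose EMDR has no true effect on a patient-rated scale, but knowledge of the arm shifts reports by b SD. With n = 36 per arm (Computation of Sample Size), the chance of a significant difference is

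Φ(b/√(2/n) − z) + Φ(−b/√(2/n) − z), with √(2/36) = 0.2357.

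For b = 0.5 and two-sided alpha 0.05: 0.5/0.2357 = 2.121, and Φ(2.121 − 1.960) = Φ(0.161) = 0.564. The second term is negligible.

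| Assumed shift b | Chance of p < 0.05 |
|---|---|
| 0 | 5.0% |
| 0.2 SD | 13.6% |
| 0.3 SD | 24.7% |
| 0.4 SD | 39.6% |
| 0.5 SD | 56.4% |

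At alpha 0.005, the level used in the sample-size section, the chance runs from 2.5% at 0.2 SD to 24.6% at 0.5 SD, against a nominal 0.5%. These figures show the exposure of a patient-rated scale to an assumed shift. They do not estimate the shift in this trial.

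**The case against.** The case on the other side is substantial.

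- **The trauma conclusion does not clearly rest on unmasked ratings alone.** A reader of Table 1 might infer that it does. Table 2 schedules EGEP-5 at T1 and T2, and the abstract points the same way. This stands: the stronger reading holds under Table 1 only, and the defect is an unresolved conflict between the tables.
- **No fixed SUD fall is built into the T1 and T2 comparison.** A reader might infer a difference of at least 6 points, or a near-certain one. The documents do not support that, because the 0 is an in-session rating of a processed memory. The protocol's own re-evaluation phase checks at the following session whether processing has held. What remains is a direction of bias of unknown size.
- **SUD may never have been meant as an efficacy outcome.** It is missing from Table 2, the abstract and the statistical analysis section. That is a fair reading. But Table 1 repeats it at T1 and T2 beside the outcome scales, and the inclusion criteria use it with IES-R to define trauma-related symptoms. Reading it as a follow-up outcome is therefore reasonable, and the protocol should exclude that reading if it is not intended.
- **Nothing is hidden.** The design section states openly that patients are not masked, so calling the trial rater-blinded is accurate. This stands.
- **EGEP-5 is not immune.** The clinician scores what an unmasked patient says. This also stands: blind scoring reduces the problem without removing it.
- **Ranking of secondary scales may sit in an analysis plan not shown.** That is so, and the lack of a ranking is not the fault found here. An analysis plan cannot recover an EGEP-5 assessment that was not made.

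**Conclusion.** The point holds in a limited form. Tables 1 and 2 contradict each other on EGEP-5 and on SUD. Under Table 1, 0 of 4 repeated trauma measures is blind-rated; under Table 2, 1 of 4 is. A SUD difference between arms at T1 or T2 is favoured by the way EMDR is delivered and should not count as independent evidence that it works, whichever table governs. How large that advantage is at T1 and T2 cannot be derived from the documents.

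This rests on three readings: that the EGEP-5 row of Table 1 carries a single mark, as printed; that the blinded clinical raters are the ones who apply EGEP-5; and that a Table 1 mark at T1 and T2 means the score is available for comparison between arms.

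The consequence is confined to the trauma part of a secondary hypothesis. Relapse is untouched, and so are the clinician-rated scales for psychotic and manic symptoms. The point should be corrected because the repair is cheap and a missed follow-up assessment cannot be recovered.

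**What to change.** 1. Correct Table 1 to match Table 2, so that EGEP-5 is applied at T1 and T2, and state that the blinded rater applies it.
2. Rest the trauma-symptom conclusion of hypothesis 2 on EGEP-5. Report IES-R, DES and SDQ-20 as supportive patient-rated outcomes.
3. Classify SUD as an entry and therapy-process measure, outside the efficacy comparison. If it is still collected at T1 and T2, describe it by arm and note its role in the therapy.
4. Say in the report that rater blinding covers the clinician-rated scales only, and that EGEP-5 still depends in part on patient report.

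The instruments and blinded raters are already in place. The cost is a table correction and an ordering of outcomes, plus EGEP-5 interviews at T1 and T2 at any site that has been following Table 1. The one real loss is that SUD is no longer available as efficacy evidence.
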